#### Functional behavior and ROM measurements

SBET measurements will be indexed to lower limb length as measured from anterior superior iliac spine to medial malleolus prior to data analysis. Two-sample t-tests with appropriate correction will be used to determine the statistical significance of differences in pre- and post-intervention ankle DF ROM, SEBT performance, and MEP/CSP data. Test-retest reliability and minimum detectable change will be determined for the 2 baseline measurements of MEP/CSP data.[37,38] Pearson correlations with appropriate statistical correction will be used to test the significance of associations among ankle DF ROM, SBET measurement, and TMS/EMG variables within subjects.

For all TMS, ROM, and lower extremity functional behaviour variables, two-factor multivariate analysis of variance with repeated measures for time will be used to determine the effects of repeated baseline testing and the intervention under study on SBET performance and ankle ROM measurements. Significant main effects will be reported if there are no significant interactions. If significant interactions are found, then one-way analysis of variance will be completed for each variable. Post-hoc testing will be performed as necessary with appropriate correction to determine the significance of pairwise comparisons. Pearson correlations with appropriate statistical correction will be used to test the significance of associations among ankle DF ROM, SBET measurement, and TMS/EMG variables within subjects.

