## Methods/Design

### Subjects

Subjects with post-acute ankle sprains (n = 27) will be enrolled into the study. Inclusion criteria include (i) subject age between 18–60 years, (ii) onset of ankle sprain at least 2 weeks prior to enrollment, (iii) Foot and Ankle Ability Measure Activity of Daily Living subscale score >20%, and (iv) ankle dorsiflexion range of motion limitation greater than 2 standard deviations from published values.[19] Exclusion criteria include (i) assisted ambulation (eg, cane or crutches); (ii) inability to bear weight through the affected extremity immediately after injury; (iii) tenderness to palpation of the medial and lateral malleolar zones, styloid process of the 5th metatarsal, and navicular[20]; (iv) positive anterior drawer or talar tilt dimple test suggesting ligamentous laxity [21-23]; (v) volume of the affected limb greater than 10% of the unaffected limb per water displacement volumetry[24]; (vi) previous history of ligament or bony reconstructive surgery to the ankle and foot; (vii) concomitant injury to other lower extremity joints; and (viii) medical conditions that serve as contraindications to mobilization/manipulation and transcranial magnetic stimulation, such as presence of pacemaker, metal in head, pregnancy, neurological disorders, recent use of stimulants or medications known to lower seizure threshold, and personal or family history of seizures.[25,26]

A total of 27 subjects will be recruited for this study (n = 9 per group). This sample size will provide >80% statistical power to detect differences in lateral star balance excursion performance based on an effect size d = 1.47 from Hale and colleagues[27] involving change in SBET score due to an exercise-based rehabilitation program in individuals with ankle sprains. Therefore, this study was powered to detect between-group differences in the selected lower extremity functional behavior following talocrural manipulation, which is thought to be the dependent variable in this study that will demonstrate the greatest intersubject variability.

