### Research Design

Subjects each begin with pre-intervention TMS measures (motor thresholds and input-output curves), ankle range of motion (ROM) tests, and lower extremity functional behavior tests. Each pre-intervention measurement will be taken a total of 2 times with a 30 minute rest break between measurements. Subjects will then be randomized into 1 of 3 comparison groups, each to receive a different manual therapy intervention. Immediately following the intervention, subjects will receive post-intervention TMS measures, ankle ROM tests, and lower extremity functional behavior tests, identical to the pre-intervention assessments.

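### The analysis rule turns to main effects when the interaction is not significant, but with randomisation after both baselines only the group-by-time contrast measures the treatment effect

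*Protocol article*

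**What the plan says.** Under Research Design, "Each pre-intervention measurement will be taken a total of 2 times with a 30 minute rest break between measurements", and "Subjects will then be randomized into 1 of 3 comparison groups, each to receive a different manual therapy intervention". The same measures are repeated once after the intervention. The Intervention section confirms that baseline recording comes before randomisation.

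Under Functional behavior and ROM measurements, a "two-factor multivariate analysis of variance with repeated measures for time will be used" for all TMS, range-of-motion and functional variables. Its stated purpose is "to determine the effects of repeated baseline testing and the intervention under study on SBET performance and ankle ROM measurements". Two rules follow: "Significant main effects will be reported if there are no significant interactions", and "If significant interactions are found, then one-way analysis of variance will be completed for each variable". The second factor is not named. With three groups and repeated time, group is the only sensible reading. The article does not say which score enters the one-way analysis (raw, post or change), nor how many time levels the model has.

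**The concern.** Testing the interaction first and reading main effects if it is null suits a factorial design whose main effects answer questions of their own. In this design neither main effect is the randomised comparison.

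- **Time main effect.** It averages over all three arms, including control, so it cannot separate treatment from practice, fatigue or drift.
- **Group main effect.** It averages the post-intervention difference with baseline differences that randomisation makes zero in expectation. It is therefore a diluted treatment effect plus chance baseline imbalance.

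The rule directs attention to these quantities exactly when the randomised comparison has shown nothing. One model is asked to speak to both repeated testing and the intervention, and no sentence says which term answers which question. A significant time effect in a trial with a null interaction could then be taken as a response to manual therapy.

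**Working it through.** **Inputs.** From the article: 9 per group, three groups, two baselines and one post measurement, randomisation after the baselines, d = 1.47, power above 80%. Assumed, because the article gives none of them: two-sided alpha .05, compound symmetry, outcome SD 1, within-subject correlation r from .5 to .9, and the sizes of practice gain. The calculations are univariate; the article's model is multivariate.

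**1. The article's own figure.** For a two-sample t-test with 9 per group and d = 1.47, the noncentral t gives 83.3% power (78.0% with 8 per group). The claim of more than 80% reproduces and is not in dispute.

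**2. Dilution of the group main effect.** Let D be an effect present only at the post measurement.
- Three time levels: (0 + 0 + D)/3 = D/3. For D = 1.47 this is 0.49.
- Baselines combined, two levels: (0 + D)/2 = D/2 = 0.735.

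With one active arm, the squared deviations of (D, 0, 0) from their mean sum to 2D²/3. The variance of a subject's three-test mean is (1 + 2r)/3. The noncentrality is 9 × (2/3) × (D/3)² ÷ [(1 + 2r)/3], which is 2.16, 1.66 and 1.54 at r = .5, .8 and .9. Power on 2 and 24 df is about 22%, 18% and 17%.

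**3. Power of the interaction at 1.47 SD.** Post minus mean baseline has variance 1.5(1 − r), so the noncentrality is 9 × (2/3) × D² ÷ [1.5(1 − r)] = 4D²/(1 − r).
- r = .5: 4 × 2.1609/.5 = 17.3, power 91% on 4 and 48 df.
- r = .8 and .9: 43.2 and 86.4, power above 99%.

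The article does not say which SD standardises 1.47. If it is the SD of a single pre-to-post change, then D² = 1.47² × 2(1 − r), the noncentrality is 17.3 at every r, and power is again 91%. If only one baseline enters the model, the same change-score effect has 87% power with one arm apart from the other two, and 75% with the middle arm halfway.

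**4. How often the main-effect branch is reached with no treatment effect.** Simulation, 20,000 trials per cell, three time levels. Gains are in SD at the second baseline / post. Entries are the percentage of trials with a null interaction and at least one significant main effect, per variable.

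| Assumed gain | r = .5 | r = .8 | r = .9 |
|---|---|---|---|
| none | 9 | 9 | 9 |
| 0.1/0.2 | 17 | 29 | 50 to 51 |
| 0.2/0.4 | 42 | 78 to 79 | 93 to 94 |

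Ranges are differences between simulation runs. The group effect stays near its nominal 5% throughout. At the low end (17%), time is significant in about 13 points; at the high end, in practically all of them. With no practice gain, the 9% is two 5% tests, one of them time.

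**5. A moderate effect: 0.5 SD in both active arms, no practice gain.** The noncentrality is 4 × 0.25/(1 − r) = 2, 5 and 10.

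| Test | r = .5 | r = .8 | r = .9 |
|---|---|---|---|
| Interaction, 4 and 48 df | 16% | 36% | 67% |
| Post minus mean baseline, 2 and 24 df | 20% | 45% | 76% |

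The omnibus interaction loses power because two of its four degrees of freedom compare the first baseline with the second, before any treatment. This loss exists only if time has three levels. At r = .8, about 49% of such trials end with a null interaction and a significant time effect.

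**The case against.** The strongest case against has five parts.

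- **The interaction is tested first.** This stands. At 1.47 SD in one arm with three time levels, a null interaction with a reportable main effect occurs in about 7% of trials at r = .5 and essentially never at r = .8. A reader might take the 17% to 22% power of the group main effect for the power of the plan. It is not: that branch is almost never reached at this effect size.
- **Time is a legitimate target.** This also stands. The model is meant to show the effect of repeated baseline testing, and the first aim is test-retest reliability. A reader might infer that the plan will announce practice effects as intervention findings, or that 94% is a false-positive rate for treatment. The article supports neither. It says that main effects will be reported, not that they will be reported as intervention effects, and a time effect produced by a real practice gain is correctly detected.
- **Practice may be reduced.** The article describes learning repetitions before the scored star balance test. That may shrink the gain for this outcome. No equivalent is described for range of motion or TMS.
- **Other analyses may cover the gap.** The two-sample t-tests of pre- and post-intervention differences might compare groups on change, but the wording does not say so. A one-way analysis of change scores by group would be the right contrast, so there is no case for dropping that step.
- **An article condenses.** Details may sit in an analysis plan that is not shown. The rule is nevertheless printed here, and as printed it attaches reporting to the wrong terms.

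**Conclusion.** The point holds as a badly fixed reporting rule, not as evidence that the trial will claim false treatment effects. Because randomisation follows both baselines, the group-by-time contrast is the treatment effect and neither main effect can stand in for it. The rule matters little if one arm differs by 1.47 SD. It matters when the effect is null or moderate: a reportable main effect beside a null interaction then arises in about 9% of trials per variable with no practice gain, and in about 17% to 94% under the assumed gains. The width of that range reflects how little the article fixes about correlation and practice. The power lost by the omnibus interaction at 0.5 SD in both active arms (4 to 9 percentage points) is secondary and depends on three time levels.

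**What to change.** Replace the main-effects rule with a statement along these lines: the treatment effect is judged only by the between-group contrast of the post-intervention value minus the mean of the two baselines, or by ANCOVA of the post value on group with mean baseline as covariate. Corrected pairwise differences with confidence intervals are reported whatever the main effects show.

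Then add three clarifications:
- Time effects are reported only as descriptions of repeated testing.
- No main effect is read as an intervention effect, and a non-significant contrast means that no treatment difference was shown.
- The one-way analysis of variance is kept and run on change scores or baseline-adjusted post scores.

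The cost is analysis wording only. Sample size, visits and measurements do not change.

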## Discussion

This study protocol describes one of the first reported feasible study methodologies to date that is designed to identify potential neuromotor changes associated with manual therapy procedures directed to the appendicular skeleton. We believe the large muscles associated with the talocrural joint and ability to localize the procedure to the talocrural joint will better elucidate potential neuromotor effects of manual therapy procedures than the studies to date that have focused on spinal procedures. Further, we will be able to compare the relative effect of treatment speed on potential neuromotor effects of manual therapy procedures in the context of a controlled study. Also, this study will provide the ability to make inferences regarding the functional relevance of changes in corticospinal excitability through the use of measurements of lower extremity range of motion and functional behavior. These characteristics will allow this study's data to further our understanding of appropriate clinical management of individuals with many forms of musculoskeletal dysfunction.

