## Abstract

**Background:**

Many health care practitioners use a variety of hands-on treatments to improve symptoms and disablement in patients with musculoskeletal pathology.

Research to date indirectly suggests a potentially broad effect of manual therapy on the neuromotor processing of functional behavior within the supraspinal central nervous system (CNS) in a manner that may be independent of modification at the level of local spinal circuits. However, the effect of treatment speed, as well as the specific mechanism and locus of CNS changes, remain unclear.

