**Discussion:**

This study is designed to identify potential neuromotor changes associated with manual therapy procedures directed to the appendicular skeleton, compare the relative effect of treatment speed on potential neuromotor effects of manual therapy procedures, and determine the behavioral relevance of potential neuromotor effects of manual therapy procedures.

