Taken together, these results suggest a potentially broad effect of manual therapy on the neuromotor processing of functional behavior within the supraspinal CNS in a manner that may be independent of modification at the level of local spinal circuits. However, several important limitations of existing studies continue to constrain our collective understanding of the CNS changes associated with the clinical effects of manual therapy in patients with musculoskeletal disablement. The use of non-disabled volunteers in the majority of existing research to date may provide limited information regarding the specific effects of mobilization and manipulation in patients with disablement due to pain and weakness. The use of spinal manual therapy as a subject of study potentially jeopardizes the specificity of conclusions that can be drawn, since spinal manipulation is poorly localized even in skilled and experienced practitioners.[18] The absence in the literature to date of behavioral measures to document potential changes in physical performance as a result of manual therapy procedures means the functional relevance of observed CNS neuroplasticity associated with cervical and lumbar manipulation also remains unclear. Also, the effect of procedure speed on CNS neuroplasticity has yet to be examined. A comparison of procedures characterized by a high velocity-low amplitude (HVLA) application of iatrogenic force with procedures that involve a slower, variable-amplitude application of iatrogenic force would be relevant, because they are among the most common clinical procedures in manual therapy.

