### Intervention

Subjects will be randomized into 3 groups after pre-participation screening is completed, informed consent is obtained, and baseline measures are recorded. The first group (n = 9) will receive an HVLA procedure directed to the talocrural joint (Figure 3). With the subject in a seated position on a treatment table and the lower extremity of interest stabilized to the table with a belt, a standardized licensed physical therapy (treating therapist) will grasp the foot of interested with the thenar eminences on the foot's plantar surface. A thrust will be delivered parallel to the long axis of the subject's lower leg after the treating therapist induces passive ankle dorsiflexion to end range. The second group (n = 9) will receive a slow procedure directed to the talocrural joint. Traction will be delivered to the talocrural joint at the treating therapist's second perception of tissue resistance in 3 bouts of 30-second holds, separated by 10 seconds of rest. The third group (n = 9) will receive the manual therapy control intervention. This will consist of the same patient and clinician preparation for the mobilization/manipulation techniques. However, the treating therapist will simply maintain passive DF ROM for the duration of 1 deep inhalation and exhalation by the subject rather than induce an iatrogenic force.

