**Figure 3 F3:**
[figure not shown]
**Ankle high-velocity low-amplitude, slow velocity, and control interventions under study**. With the subject in a supine position on a treatment table and the lower extremity of interest stabilized to the table with a belt (A), the treating investigator will grasp the foot of interested with the thenar eminences on the foot's plantar surface (B) and induce passive dorsiflexion to end range (B; open arrow). Iatrogenic force will be provided along the long axis of the tibia in the intervention groups. (B; hatched line) In the control group, the treating investigator will maintain passive dorsiflexion (B; open arrow) for the duration of 1 deep inhalation and exhalation by the subject rather than induce an iatrogenic force.

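### The trial claims to compare treatment speed, but its fast and slow arms also differ in number of applications and time under force

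*Protocol article*

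**What the plan says.** The claim about speed appears twice in the protocol article. The Discussion says "we will be able to compare the relative effect of treatment speed on potential neuromotor effects of manual therapy procedures". The Discussion paragraph of the Abstract gives as one of the study's purposes to "compare the relative effect of treatment speed on potential neuromotor effects of manual therapy procedures".

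Both follow from how the question is posed. The Abstract's Background says that "the effect of treatment speed, as well as the specific mechanism and locus of CNS changes, remain unclear", and the main Background says that "the effect of procedure speed on CNS neuroplasticity has yet to be examined". The Background then names the contrast of interest: HVLA procedures against "procedures that involve a slower, variable-amplitude application of iatrogenic force".

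The Intervention section defines the arms. For the HVLA arm, "A thrust will be delivered parallel to the long axis" of the lower leg once the ankle has been taken passively to the end of dorsiflexion; no repeats are described. The slow arm receives traction at the second perceived tissue resistance, "in 3 bouts of 30-second holds, separated by 10 seconds of rest". The control arm holds passive dorsiflexion for one breath without added force. The Figure 3 caption says that "Iatrogenic force will be provided along the long axis of the tibia in the intervention groups", so the two active arms share the direction of force.

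Specific aims 2 and 3, at the end of the Background, refer to HVLA, slow and control interventions by name and do not mention an effect of speed.

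**The concern.** To attribute a difference between two arms to one feature, the arms must be alike in the other features that could plausibly produce it, or the design must contain some means of separating them. Randomization balances the subjects; it does not balance the components of the procedures. Here the only fast-versus-slow contrast changes speed, number of applications and duration of force together.

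This affects both possible results. If the HVLA and slow arms differ, the cause could be three applications instead of one. If they do not differ, a speed effect could have been offset by the greater number and duration of applications. The article presents speed as an open mechanistic question and says in the Background that a better understanding of mechanism across speeds and amplitudes should improve patient selection. A reader would therefore naturally take the HVLA–slow result as the answer on speed, which it cannot be.

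**Working it through.** The article gives no numerical figure for this point to reproduce. The check sets the two active arms side by side, using the Intervention section, the Figure 3 caption and the Background.

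| Feature | HVLA arm | Slow arm | Matched? |
|---|---|---|---|
| Direction of force (Figure 3 caption) | long axis of the tibia | long axis of the tibia | yes |
| Speed | thrust | sustained traction | no, by intention |
| Number of applications | 1 | 3 | no |
| Time under force | one thrust, duration not stated | 90 s | no |
| Amplitude | not stated for the arm; low by class description | not stated for the arm; variable by class description | cannot be established |

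**Slow-arm dose.**

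- Time under traction = holds × length of hold = 3 × 30 s = 90 s.
- Elapsed time = traction + rests = 3 × 30 s + 2 × 10 s = 110 s.

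**How much of this is inherent in being slow.** A sustained hold necessarily lasts longer than a thrust, so grant that the first 30-second hold belongs to the definition of the slow procedure. The second and third holds do not: a single hold would be delivered at the same speed.

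- Traction time from repetition = (3 − 1) × 30 s = 60 s.
- Share of all traction time = 60 / 90 = 67%.

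No duration ratio between the arms is given, because the length of the thrust is not stated.

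**Whether anything else in the design separates the features.**

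- The control arm applies no added force and lasts one breath. It matches neither active arm in number of applications or duration of force, so it cannot separate those features from speed.
- The Data Analysis section compares groups over time and contains no term for dose or for speed. With one fixed dose per arm, none could be estimated: number of applications is fully determined by arm.

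The HVLA–slow contrast therefore identifies the difference between two whole procedures and nothing narrower.

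**The case against.** The strongest reply is that treatment speed is shorthand for two classes of procedure. Immediately after noting that the effect of speed is unexamined, the Background says which comparison would be relevant, describes the slow class as variable in amplitude, and justifies the choice by how common both classes are in practice. On that reading the contrast is openly one of packages. Nothing operative turns on the phrase: the aims name the procedures, the arms are fully described, and no test is labelled a test of speed.

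Much of this stands. Comparing the procedures as clinical packages is legitimate, and no estimate or test is invalidated. Part of the duration difference is inherent in sustained traction. The 67% split depends on counting one hold as the slow procedure; a single 90-second hold would give the same time under force without repetition. The figure describes the dose and does not measure bias. The article also offers no evidence that repetition changes corticospinal excitability, or in which direction, so the offsetting scenario is a possibility and not a prediction. Amplitude should not be pressed, since neither arm's value is given and an article may leave that to the full protocol.

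The shorthand reading still does not rescue the sentences. The Background places procedures on a scale of speed and amplitude, treating speed as a dimension in its own right, and poses the effect of speed as the gap in knowledge. The accurate wording, naming the procedures, is already used in the aims; the Abstract and Discussion go beyond it. The point does not depend on anything left out of a condensed article, because the doses that conflict with the claim are stated.

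**Conclusion.** The concern holds. The Abstract and the Discussion attribute to the design a comparison of speed that it cannot make: one thrust is set against three holds totalling 90 seconds of traction, and neither another arm nor the planned analysis separates speed from number of applications or time under force.

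The severity is minor. The error is in the stated inference; aims 2 and 3, the procedures and the between-group comparison remain sound. The conclusion assumes that the HVLA arm receives a single thrust, as the singular wording indicates. It needs no assumption about thrust duration, amplitude or the size of any effect of repetition.

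**What to change.** In the Discussion paragraph of the Abstract and in the main Discussion, replace the statement about speed with one along these lines: *the study will compare the neuromotor effects of a single HVLA thrust with those of a slow sustained-traction procedure, each as delivered in this trial.*

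Add one sentence fixed in advance of the results: *a difference between these two arms, or the absence of one, will not be attributed to speed alone, because the number of applications and the duration of force also differ.*

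The statements in the Abstract's Background and in the main Background can stay, since they describe what is unknown and not what this trial will show. Procedures, aims, sample size and analysis need no change. The cost is two reworded sentences, one added sentence and a narrower claim.
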